##### Socio-demographic characteristics

We will ask patients to report demographic information that is not available in the medical record, such as marital status, years of education, occupation, and household income. We will collect the following characteristics for clinicians: type of practice, years in practice and at practice site, gender, birth year, ethnicity, race, estimate of time in direct patient care, proportion of practice devoted to patients with diabetes, and average length of appointments with diabetes patients. Data will be collected to characterize participating practices including race, ethnicity, and insurance status of patients seen in the practice; practice type, community size, and make-up of staff including clinicians, allied health staff, and patient educators.

##### Sample size

A total of 8 practices will be randomized to 1) the Diabetes Medication Choice decision aid plus statin and aspirin usual care or 2) the Statin Choice and Aspirin Choice decision aids plus diabetes medication usual care. The Statin Choice cluster randomized trial evaluated decision quality comparing the decision aid to usual care. This study reported a 9.8 point difference in decision quality^3^ with the standard deviation of 16.9 and 14.1 for the usual care and decision aid groups, respectively. Making the following assumptions: 1) variances are as reported in this study; 2) we seek to detect a difference of 9.8 points or greater in decision quality between two groups at significance level of 0.05, with a two-sided *t*-test; 3) a modest correlation of outcomes across these clinicians and practices (which is a conservative assumption) represented by an intracluster correlation coefficient (ICC = between cluster variance/total variance) of 0.05; 4) a variance inflation or design effect factor [1+ (n − 1) · ICC], where n is the number of patients per cluster [31]; and 5) an approximated 20% attrition rate, we will have 80% power if we are able to recruit 30 patients per clinic for a total recruitment target of 240 patients. Assuming a similar ICC and attrition rate for other outcomes, this sample size will have 99% power to detect a 1 SD difference in any continuous measure (e.g., approximately a 2-point difference in a 10-question knowledge scale), and 80% power to detect a 30% difference in 6-month adherence rates assuming a control adherence rate of 50%. Actual power will be likely greater because we will adjust for baseline values and characteristics and because of our conservative assumptions.

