### Allocation procedures

Randomization will be by practice. The study will compare the use of the decision aids within the clinical encounter versus usual care. We will identify pairs of practices that are most similar in size (i.e., number of clinicians seeing adult patients with type 2 diabetes) and randomize within each pair to use either the 1) the *Statin Choice* and the *Aspirin Choice*, or 2) the *Diabetes Medication Choice* decision aid. Each practice will also serve as the usual care arm for the other intervention arm (Figure 2). This approach will seek to ensure similar representation of ‘easy’ and ‘difficult’ practices in both decision aid groups and eliminate the need for any site to simply serve as a usual care arm. A study statistician will perform the randomization centrally after the practices have been enrolled, ensuring concealment of allocation of the paired practices. Practices, clinicians, patients, and investigators will not be masked to the intervention. However, patients providing outcomes will remain masked to their practice status, as consent documents will keep patients unaware of the study’s main hypotheses. Furthermore, we will centrally follow patients and ensure that patient surveys and pharmacy follow-up are completed according to the intention-to-treat principle.

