##### Outcomes measures

To assess *Effectiveness* of the decision aids (R**E**-AIM) we will measure the decisional conflict as the primary outcome and patient involvement in decision making, diabetes care processes, medication adherence, glycemic and cardiovascular risk factor control, and resource utilization as secondary outcomes, in the following way:

· *Patients’ decisional conflict*. Patients will complete, immediately after the clinical encounter with their clinician, a modified version of the Decisional Conflict Scale [15], the most commonly used outcome measure in decision aid trials [5]. These modifications entail the use of brief items that explore the quality of the deliberation process during the visit. Psychometric properties include good internal consistency, test–retest reliability, and effect sizes for responsiveness to change ranging from 0.4 to 1.2 [15,16].

· *Patients’ involvement in decision making*. We will use the OPTION scale to assess the extent to which clinicians seek to engage patients in decision making [17,18]. OPTION is a third-person observer scale and was designed for use in reviewing audio recordings of primary care visits. Our group has extended the use of this tool to video recordings with excellent inter-rater reliability (intraclass correlation coefficient >0.7) [6,19,20].

· *Patients’ knowledge*. Patients will complete a knowledge questionnaire immediately following the encounter with their clinicians, and at 3 and 6 months post-encounter. The questionnaire was developed according to prior recommendations and is similar to questionnaires used in our previous studies, addressing general knowledge about diabetes and lipid management and specific information contained in the decision aids [6,8].

· *Patients’ satisfaction*. Satisfaction with decision making will be assessed using items from the Decisional Conflict Scale [15] as well as two specific questions that require patients to assess the extent to which they would want for themselves and recommend to others similar decision support as they received during the visit. Other questionnaires exist to specifically address this domain, but our use of the Decisional Conflict Scale for this purpose reflects our effort to minimize participant burden.

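### The stated 80% power is not supported by the calculation shown, which allows neither for only eight randomised practices nor for each practice supplying both arms

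*Protocol article*

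**What the plan says.** The Sample size section under Aim 1 takes its effect and spread from an earlier cluster trial of the statin aid. It states that "we seek to detect a difference of 9.8 points or greater in decision quality between two groups". The test is a two-sided t-test at the 0.05 level, and the spread is a "standard deviation of 16.9 and 14.1 for the usual care and decision aid groups, respectively". Clustering is "represented by an intracluster correlation coefficient (ICC = between cluster variance/total variance) of 0.05" and enters through the usual design effect, 1 + (n - 1) x ICC. Attrition is put at 20%. The result is that "we will have 80% power if we are able to recruit 30 patients per clinic for a total recruitment target of 240 patients".

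The section then claims 99% power for a 1 SD difference in any continuous measure and 80% power for a 30-point difference in adherence from a control rate of 50%. It closes by saying that "Actual power will be likely greater because we will adjust for baseline values and characteristics", and also cites its conservative assumptions.

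Three other sections bear on this:

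- Allocation procedures randomises practices within pairs and adds that "Each practice will also serve as the usual care arm for the other intervention arm".
- The Aim 1 Analysis section groups patients into arms by whether an aid was used in the encounter. It estimates effects by random-effects meta-analysis over the matched pairs, of which it says there are five.
- Outcomes measures describes the primary outcome thus: "Patients will complete, immediately after the clinical encounter with their clinician, a modified version of the Decisional Conflict Scale".

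**The concern.** A design effect inflates the variance for clustering, but it does not correct the degrees of freedom. With eight randomised practices, the reference distribution for a valid cluster-level test is a t with few df. The critical value is 2.45 on 6 df (pairs broken) or 3.18 on 3 df (four pairs kept), against 1.99 on the roughly 76 df implicit in the stated figure.

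The formula also models a trial in which each practice belongs wholly to one arm. This trial has each practice contribute to both, so part of the practice effect cancels, and the design effect as applied does not describe it.

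The 80% is the figure offered to justify the trial's size. If it cannot be relied on, a non-significant primary result could be read as stronger evidence against the aids than the design can give. The article already calls attention to the small number of clusters when it chooses its baseline test and when it discusses estimating the ICC, but not in the power calculation.

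**Working it through.** **Inputs** (Sample size section unless stated): difference 9.8; SDs 16.9 and 14.1; two-sided 0.05; ICC 0.05; 8 practices, so 4 per arm in the one-arm layout; 30 recruited per practice; 20% attrition. Pairing and dual role are from Allocation procedures.

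**1. Reproducing the plan's figure.**

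- SD = sqrt((16.9² + 14.1²)/2) = sqrt(242.21) = 15.56.
- Retained: 30 x 0.8 = 24 per practice; 4 x 24 = 96 per arm.
- Design effect at n = 30: 1 + 29 x 0.05 = 2.45. Effective patients per arm: 96/2.45 = 39.2.
- SE = 15.56 x sqrt(2/39.2) = 3.516. Noncentrality = 9.8/3.516 = 2.787.
- Power = 79.6% (normal) or 78.6% (t, 2 x 39.2 - 2 = about 76 df).
- In reverse: 40 independent patients per arm x 2.45/0.8 x 2 = 245, against 240 stated.

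With the design effect applied to the 24 retained patients it is 1 + 23 x 0.05 = 2.15. Effective patients are then 44.7, noncentrality 2.975, and power 84.5% or 83.7%. There is no slip in the arithmetic.

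**2. Same layout, same noncentrality, cluster-level df.**

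| Design effect | 6 df | 3 df |
|---|---|---|
| 2.45 | 64.4% | 48.0% |
| 2.15 | 70.0% | 52.7% |

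The 3 df column credits matching with no reduction in between-practice variance. At design effect 2.15, removing half of that variance gives 65%, and removing all of it gives 83%.

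**3. The other two claims, same layout.** For 1 SD, noncentrality is sqrt(39.2/2) = 4.43 or sqrt(44.7/2) = 4.73. Power is 99.3-99.7% on independent patients, 95-97% on 6 df and 83-87% on 3 df. For adherence 50% against 80%, the SE is sqrt((0.25 + 0.16)/n_eff). Power is 69-74% on 6 df and 52-56% on 3 df.

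**4. Dual-role layout.** Assume each practice's 24 retained patients divide between the two topics, with h on one topic and 24 - h on the other. The split is an assumption; the article does not give it. Between-practice variance is 0.05 x 242.21 = 12.11, of which a share s is specific to the topic (also not given). For a practice with a aid patients and b usual-care patients, the aid-minus-usual difference has variance

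V = 0.95 x (14.1²/a + 16.9²/b) + 2 x 12.11 x s.

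Averaging over four practices of each kind gives SE = sqrt((V1 + V2)/16). For 12/12 and s = 0: V = 0.95 x 484.42/12 = 38.35, SE = 2.189, noncentrality 4.48. For s = 1: V = 38.35 + 24.22 = 62.57, SE = 2.797, noncentrality 3.50.

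| Split | 6 df, s = 1 to s = 0 | 3 df, s = 1 to s = 0 |
|---|---|---|
| 12/12 | 83-96% | 65-83% |
| 8/16 | 80-94% | 62-79% |
| 4/20 | 67-79% | 50-61% |

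**5. The planned random-effects pooling, simulated over four pairs** (40,000 runs, 24 retained per practice, DerSimonian-Laird estimate). In the one-arm layout with a z reference it rejects in 82% of runs, but its type I error is 9.8%. Held to a true 5% its power is about 69%, and with a Hartung-Knapp t reference 53%. In the 12/12 dual-role layout the z reference has type I error 4.3-7.8%. Power at a true 5% is then 85-98%, and Hartung-Knapp gives 65-84%.

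**6. Number of pairs.** Eight practices in pairs make four strata, but the Analysis section says five. Five pairs sharing 240 patients would give 79% (8 df) or 66% (4 df) in the one-arm layout.

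**7. Baseline and scale.** The Sample size section expects power to gain from baseline values. Outcomes measures places decisional conflict only after the visit, so no baseline value of the primary outcome is described. The 9.8 points and SDs are for decision quality, the primary outcome is a modified decisional conflict scale, and the link between them is not stated.

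**The case against.** The strongest reply is that the arithmetic is right for the method stated, and that the low figures in step 2 belong to a layout this trial does not use. Both points stand. A reader might infer from step 2 that the trial is underpowered and that eight practices cannot deliver 80%. The documents do not support that. With an even split, every dual-role result on 6 df is above 80%, and even on 3 df power reaches 83% if practice effects are fully shared between topics. The split, the shared variance and the reference distribution are all unstated.

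It is also fair that a paired t-test on 3 df is not the named analysis. The named one is random-effects pooling, for which the article gives no reference distribution. Simulated with a z reference it appears to recover 80% in the one-arm layout, but only at a type I error near 10%, so that result does not validate the stated figure.

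On baseline adjustment, one might infer that the claim of extra power is simply false for the primary outcome. That goes too far. The sentence also names baseline characteristics and conservative assumptions, and adjusting for characteristics needs no prior score. Only the part resting on baseline values fails for decisional conflict. Nor do the documents show that the 9.8 points come from the wrong instrument, only that the instrument is not identified.

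Finally, the abstract presents the trial as giving a preliminary estimate, and the analysis promises confidence intervals. That softens the consequence but leaves the stated figure uncorrected.

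**Conclusion.** The concern holds in this form: the stated 80% is unsupported by the calculation shown, for either layout. The calculation treats 39.2 effective patients per arm as independent and places each practice in one arm. On its own layout, with cluster-level df, the plan's inputs give 64-70% or 48-53%. On the dual-role layout, the splits examined run from 50% to 96%, so true power could be under or over 80%. The 99% and 80% claims for other outcomes were reached the same way and need the same recomputation.

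These ranges rest on the plan's ICC of 0.05 and 24 retained patients per practice, on four pairs, and on assumed topic splits and shared variance. The missing-data text assumes 10% loss rather than 20%. At 27 retained per practice the one-arm figures are 69-72% (6 df) or 52-55% (3 df), so that inconsistency does not change the conclusion.

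**What to change.** Rewrite the Sample size paragraph:

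- Recompute all three power figures for the planned pooled analysis with each practice in both arms, using a small-sample reference distribution. Show the range over the topic split and over how far practice effects are shared between topics.
- Reconcile eight practices in pairs with the five strata in the Analysis section, because the degrees of freedom depend on it.
- Limit the sentence on greater power to adjustment for baseline characteristics and to outcomes that have a baseline value.
- State whether the 9.8 points and the SDs are on the decisional conflict scale used as the primary outcome.

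The cost is one paragraph and a short recalculation. No extra patients are needed; the stated power may become less favourable.

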##### Analysis

We will have a summary of the cluster level and patient level characteristics within each trial arm, providing counts and frequencies for categorical variables and means with ranges for continuous variables. Because of the uncertainty as to the ability of a cluster trial to create uniform prognostic groups, we will test the null hypothesis of no difference between arms in baseline cluster level characteristics using the weighted paired *t*-test [32]. This test can account for the small number of clusters and an unequal number of patients within each cluster.

To account for the modified study design (e.g., each arm being both intervention and usual care), the study team assumes similar adherence rates within statin medications and diabetes medications along with similar knowledge, decisional conflict, and satisfaction rates for patients discussing either medication for those within the usual care group. For the decision aids (Statin, Aspirin and Diabetes Medication) the study team assumes the same impact on all of these outcomes for all decision aids. With these assumptions, all patients that use a decision aid during the encounter of interest will be grouped in the decision aid arm and those that do not will be grouped under the usual care arm. To account for differences that may exist between the diabetes, statin, and aspirin patients, all models will be adjusted by group. Interaction between arm and group will be tested for significance, recognizing that the study will be underpowered to test for this interaction.

To evaluate the efficacy of the intervention, differences in all patient level outcomes, for both continuous and dichotomous outcomes (as well as patient characteristics at baseline) will be estimated using the random effects meta-analysis method [31]. This approach has been validated for matched pair cluster-based studies: differences in means for continuous outcomes and in proportions for dichotomous outcomes are estimated and then pooled across strata. A stratum in terms of a matched-pair study is considered to be each pair, and in this trial there are 5 strata. For each outcome, we will thus estimate the effect size and its precision (e.g., 95% confidence interval). The outcomes will be assessed at baseline, 3 and 6 months. We will estimate the intraclass correlation coefficient for each outcome along with its 95% confidence interval and report these for informational purposes only since the number of clusters is insufficient to determine with confidence a true intraclass correlation^124^. Within patients that had a diabetes medication discussion, HbA1c will be collected and categorized to <7.3 versus ≥7.3. This outcome will be analyzed as described above for categorical outcomes. All analysis and data management will be conducted utilizing SAS (version 9, Cary, NC) with use of Stata statistical software (version 11.0, College Station, Tx) for primary endpoint analysis.

Patients with missing outcome data will not be included in assessment of that particular outcome. We will compare the incidence of missing data for each outcome between study arms, both absolutely and as a function of follow-up period. We will report rates of missing data for each outcome by study arm and known reasons for missing data. In the event that the rate of missing data is not independent of study arm or is greater than the assumed 10% loss to follow-up, we will conduct sensitivity analyses under a range of assumptions about the missing values and assess consistency of results across those scenarios. In the event that patients are missing baseline characteristics data, which are otherwise imbalanced between the two study groups, we will use imputations to estimate models which include those characteristics.

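### The baseline test on four pairs of practices cannot show comparability, and a separate rule lets observed imbalance decide which baseline characteristics are modelled

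*Protocol article*

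**What the plan says.** All references are to the protocol article.

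- **Description.** The Analysis section under Aim 1 opens with a descriptive plan: "We will have a summary of the cluster level and patient level characteristics within each trial arm".
- **Test.** It then doubts whether a cluster trial yields prognostically similar groups, and for that reason plans a test: "we will test the null hypothesis of no difference between arms in baseline cluster level characteristics using the weighted paired" t-test. The reassurance offered is: "This test can account for the small number of clusters and an unequal number of patients within each cluster". No significance level, margin or consequence is attached to the result.
- **Number of pairs.** Sample size: "A total of 8 practices will be randomized to" one decision aid package or the other. Allocation procedures: "We will identify pairs of practices that are most similar in size", with randomisation inside each pair. That gives four pairs. The Analysis section equates a stratum with a pair but counts five strata.
- **Arms.** Under Allocation procedures, each practice uses the aid for one medication topic and provides usual care for the other. The Analysis section then pools: "all patients that use a decision aid during the encounter of interest will be grouped in the decision aid arm", and the remaining patients form usual care. All models are adjusted for medication group.
- **Missing baseline data.** Where patients lack baseline characteristics, "which are otherwise imbalanced between the two study groups, we will use imputations to estimate models which include those characteristics". How imbalance is to be recognised is not stated.

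**The concern.** There are two separate problems.

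First, the section asks whether the groups are alike and answers with a test of no difference. Failing to reject is not a demonstration of similarity, least of all with four pairs. The remark that the test copes with few clusters is about its validity (type I error). It says nothing about its ability to detect an imbalance. Under proper randomisation any difference is due to chance anyway, so what matters is how large it is and whether the characteristic is prognostic.

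Second, the missing-data rule lets the observed baseline data decide which characteristics lead to imputation and enter a model. A strongly prognostic characteristic that happens to look balanced may be left out, and a weak one that looks unbalanced may be brought in. The model then depends on the sample, with no stated threshold.

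**Working it through.** **The plan's own figure.** The article gives no power for the baseline test. Its sample-size claim does reproduce: SD = √((16.9² + 14.1²)/2) = 15.56; design effect 1 + 29 × 0.05 = 2.45; 192 completers give 96/2.45 = 39.2 effective patients per arm; power for 9.8 points is 79.6% (normal approximation) against the stated 80%. That calculation concerns the outcome and does not bear on the baseline test.

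**Inputs for the baseline test**
- Pairs: k = 8/2 = 4 (Sample size; Allocation procedures), so df = 3. Five pairs are also shown because of the five strata.
- Level: two-sided 5%. This is stated for the outcome comparison and assumed here.
- Within-pair correlation ρ of the characteristic: not given, so varied from 0 to 0.9. Pairs are matched on size, so size-related characteristics may lie at the upper end.
- Equal weights, checked below.

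**Formula.** In units of the between-practice SD, a pair difference has SD √(2(1−ρ)). For a true difference d, the noncentrality is d√k/√(2(1−ρ)). Power comes from the noncentral t with k−1 df.

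**Result for d = 0.5 SD**

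| ρ | Noncentrality (4 pairs) | Power (4 pairs) | Missed (4 pairs) | Missed (5 pairs) |
|---|---|---|---|---|
| 0 | 0.707 | 8.1% | 91.9% | 90.5% |
| 0.5 | 1.000 | 11.1% | 88.9% | 86.0% |
| 0.7 | 1.291 | 15.2% | 84.8% | 79.9% |
| 0.8 | 1.581 | 20.2% | 79.8% | 72.4% |
| 0.9 | 2.236 | 34.3% | 65.7% | 52.3% |

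A true 1-SD difference is missed 82.8% of the time at ρ = 0 and 71.1% at ρ = 0.5. With four pairs, 80% power needs a difference of 3.01 SD (ρ = 0) or 2.13 SD (ρ = 0.5).

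**Unequal weights.** Simulation with pair weights 1.5:1:1:0.7 and 2:1:1:0.5 gives power of 7.2-7.8% at ρ = 0 and 9.9-10.6% at ρ = 0.5, slightly lower than with equal weights.

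**Realised imbalance.** The table concerns a true mean difference. If the observed difference is exactly 0.5 SD, four pairs give significance only if the sample SD of the pair differences is below 0.5 × √4/3.182 = 0.314. The result is then non-significant in 98.5% of cases (ρ = 0), 96.1% (ρ = 0.5) or 86.4% (ρ = 0.8).

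**How often chance produces it.** P(|difference| ≥ 0.5 SD) = 2[1 − Φ(0.5/√(2(1−ρ)/4))], which is 48% at ρ = 0 and 32% at ρ = 0.5, for any one characteristic.

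**Check without a t distribution.** Four pairs allow 2⁴ = 16 assignments, so an exact within-pair randomisation test has a smallest two-sided p of 2/16 = 0.125. With five pairs it is 2/32 = 0.0625. Neither reaches 0.05.

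**Which contrast is tested.** By assignment, the two randomised sets of practices are the two sides of the comparison within diabetes-medication patients, and again within statin/aspirin patients. In the pooled aid versus usual-care comparison, all eight practices contribute to both sides.

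**The case against.** The strongest reply is that nothing in the article hangs on this test. That stands. A reader might infer that a non-significant result would keep a characteristic out of the adjusted models, but the text does not support this. The test is on practice-level characteristics. The imputation rule concerns patients with missing baseline data, and imbalance there is not defined by this test or by any p-value. Patient baseline differences are estimated by a separate route, the random effects meta-analysis, and Sample size states without condition that baseline values and characteristics will be adjusted for. Nor does the article say that non-significance will be reported as comparability, and a descriptive summary is already planned.

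A reader might also infer that the test compares the wrong groups. That is too strong. Practices are the randomised units, models are adjusted for medication group, and within a topic the two sets are the two sides, apart from patients with whom the aid is not used. The mismatch holds for the pooled comparison only.

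The 89-92% range is not the article's and rests on assumptions. Closer matching lowers it, and a half-SD scale does not suit categorical practice characteristics such as practice type. These limits narrow the statement but do not make the test informative.

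Finally, a covariate list is commonly left to an analysis plan, which is not shown. Its absence is not the complaint. The complaint is the imbalance-driven rule that the article does state.

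**Conclusion.** The point holds in limited form and is minor. A test on four pairs cannot answer the question for which it is introduced. At a two-sided 5% level it misses a true 0.5-SD difference about 89-92% of the time for within-pair correlation 0 to 0.5, and 66-85% for 0.7 to 0.9. If there were five pairs, the first range would be 86-91%. The level and the correlations are assumptions, but over the whole range considered a non-significant result is no evidence of comparability. Removing the test would by itself change no trial result.

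The more useful finding is the separate one: imputation and models with baseline characteristics depend on observed, undefined imbalance among patients. That is a data-dependent rule whether or not the practice-level test is kept.

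**What to change.** 1. In the Analysis section, delete the hypothesis test on practice-level characteristics. Keep the descriptive summary and report the size of each difference between the two randomised sets of practices, without p-values. State that these sets are the two sides within each medication topic but not in the pooled aid versus usual-care comparison.
2. In the missing-data paragraph, replace the imbalance trigger with a short list of covariates chosen on prognostic grounds and fixed before outcome data are seen. Impute missing values of those covariates regardless of observed imbalance.
3. Reconcile the five strata with eight practices randomised in pairs.

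The cost is wording, and one analysis fewer. The small downside is having to commit to the covariate list in advance.

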#### Training of clinicians

A study team member will conduct a demonstration showing how to use the decision aid at the time of the initial in-person discussion with clinics. The focal points of the demonstration will be that decision aids serve as guides for conversation rather than scripted discussions; that clinicians have flexibility in the manner in which they use the decision aid, including how and when they use them during the visit; and that they may elect not to use the tools with certain enrolled patients, per their own judgment. Brief video clips and storyboards that demonstrate the basic use of decision aids are publicly available at http://kercards.e-bm.info for clinicians to review at their convenience. A study team member will remain available to do one-on-one demonstrations after the initial group demonstration if needed.

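### As written, the analysis arms are formed by whether the aid was used, which clinicians may decide patient by patient, so the primary comparison is as-treated for patients whose aid is skipped

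*Protocol article*

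**What the plan says.** Allocation is at practice level, within matched pairs: "Randomization will be by practice" (Allocation procedures). Each practice receives one tool and serves as usual care for the other topic. The allocation is open: "Practices, clinicians, patients, and investigators will not be masked to the intervention".

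Clinicians are told in training that "they may elect not to use the tools with certain enrolled patients, per their own judgment" (Training of clinicians).

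The Analysis section for Aim 1 then forms two pooled groups. The first is defined by use: "all patients that use a decision aid during the encounter of interest will be grouped in the decision aid arm". For the remaining patients the same sentence sets the comparator group, in these words: "those that do not will be grouped under the usual care arm". Models are adjusted by group (diabetes, statin, aspirin). The same section estimates the differences in all patient-level outcomes, which include the primary one: "we will measure the decisional conflict as the primary outcome" (Outcomes measures).

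Intention to treat appears once, in Allocation procedures, where the team undertakes to "ensure that patient surveys and pharmacy follow-up are completed according to the intention-to-treat principle". That sentence concerns completeness of follow-up. It does not say in which arm a patient is analysed.

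**The concern.** Taken together, the training and analysis sections let an unmasked clinician determine a patient's analysis arm during the visit. If the practice was randomised to the aid for the topic discussed and the clinician leaves it out, the patient moves from the randomised aid arm to usual care. For that fraction the comparison is as-treated, and any prognostic difference between patients who are and are not shown the aid enters the effect estimate. Adjusting for diabetes, statin or aspirin group does not remove selection by clinicians within a practice. Moving non-users can also put both analysis arms in one practice for the same topic, which does not fit an estimator that pools differences between the two practices of a pair.

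At stake are the primary comparison on decisional conflict and the secondary patient-level outcomes that use the same arms. In a practical trial, the effectiveness estimate would also leave out the consequence of incomplete uptake.

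**Working it through.** **Inputs from the Sample size section.** SDs 16.9 (usual care) and 14.1 (decision aid); target difference 9.8 points; two-sided 5% level; ICC 0.05; 8 practices of 30 patients; 20% attrition; stated power 80%. That section words the target as decision quality: "we seek to detect a difference of 9.8 points or greater in decision quality between two groups". I use the same 9.8-point scale for the primary outcome.

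**Inputs not in the article (assumptions).** The share q of patients in aid encounters for whom the aid is not used, taken as 0 to 30%. The prognostic gap δ between would-be users and would-be non-users, taken as 0.25 to 0.5 SD. The usual-care patients are assumed to contain the same mix of the two types.

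**1. Reproduce the stated power.**
- SD = √((16.9² + 14.1²)/2) = 15.56.
- Design effect = 1 + (30 − 1) × 0.05 = 2.45.
- Completers per arm = 4 × 30 × 0.8 = 96; effective n = 96/2.45 = 39.2.
- SE = 15.56 × √(2/39.2) = 3.52.
- Power = Φ(9.8/3.52 − 1.96) = 79.6%.

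The 80% is reproduced, for two equal arms with no patient moved between them.

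**2. Spurious difference when the aid has no effect.** Set the overall mean to zero and let users and non-users differ by δ.
- Mean of users: qδ.
- Mean of non-users: −(1 − q)δ.
- Mean of the enlarged usual-care group (weight 1 at zero, weight q at −(1 − q)δ): −q(1 − q)δ/(1 + q).
- Difference: qδ + q(1 − q)δ/(1 + q) = 2qδ/(1 + q).

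Example, q = 0.2 and δ = 0.5 SD: 2 × 0.2 × 0.5/1.2 = 0.167 SD, or 2.6 points. The sign reverses if the skipped patients are those who would have done better.

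**3. Type I error.** Moving patients makes the arms unequal: 96(1 − q) and 96(1 + q). So SE = 15.56 × √(2.45 × [1/(96(1 − q)) + 1/(96(1 + q))]), and the two-sided error is P(|Z + bias/SE| > 1.96). This is a normal approximation at patient level that ignores the pairing.

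**4. Power if arms follow assignment.** If users gain the full 9.8 points and non-users nothing, the difference is 9.8(1 − q), with SE 3.52.

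| Non-use q | Bias, δ = 0.25 SD (points) | Bias, δ = 0.5 SD (points; share of 9.8) | SE by use | Type I error, δ = 0.25 | Type I error, δ = 0.5 | Power by assignment |
|---|---|---|---|---|---|---|
| 0% | 0 | 0 | 3.52 | 5% | 5% | 79.6% |
| 10% | 0.7 | 1.4 (14%) | 3.53 | 5.5% | 6.9% | 70.8% |
| 20% | 1.3 | 2.6 (26%) | 3.59 | 6.5% | 11.2% | 60.6% |
| 30% | 1.8 | 3.6 (37%) | 3.69 | 7.8% | 16.4% | 49.6% |

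Biases are absolute sizes. The two-sided error is the same for either sign.

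**The case against.** The best defence is that *use* is this article's word for allocation. Practices are randomised to use one tool or the other, and the intervention is defined as use of an aid. The disputed sentence comes in a paragraph about pooling three aids and two topics under two labels, and that paragraph does not discuss non-adherence. Figure 2, on eligibility and assignment by arms, is not reproduced in the text reviewed and may already fix each patient's arm at enrolment. So a reader who infers that the authors intended an as-treated analysis goes beyond the documents. What remains is that the sentence ties use to the individual visit, the training section separates enrolment from use, and nothing in the text corrects the literal reading. Under either intent the sentence needs the same edit.

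Other stronger readings also fail:

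- *The plan contradicts its own intention-to-treat commitment.* That commitment is attached only to follow-up completion, so there is a gap and no flat contradiction.
- *The bias favours the aid.* The article says only that clinicians use their judgment. They might skip hesitant patients, or patients already settled on a choice. The direction is not given.
- *Usual-care patients cross over to the aid as well.* No section describes this, and the Usual care section excludes use of the aids.
- *Every result becomes purely observational.* Practice randomisation still governs access to each aid; only the fraction whose aid is skipped is affected.
- *Poor uptake would go unseen.* Adoption and fidelity are measured separately. Only the effect estimate omits uptake.

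**Conclusion.** The point stands on the text. Followed literally, the plan gives a primary comparison that is as-treated for patients whose clinician leaves the aid unused, and it describes no comparison by assignment. The bias is nil at full uptake, grows with non-use, and can go either way. Over 10 to 30% non-use and a gap of 0.25 to 0.5 SD it runs from 0.7 to 3.6 points. At the 0.5 SD gap, type I error is about 7%, 11% and 16% at 10%, 20% and 30% non-use. Keeping the equal-arm SE of 3.52 would give 17.5% for the last of these, which overstates it because moving patients makes the arms unequal. Both the non-use rate and the gap are assumptions, so these figures illustrate a range and do not predict this trial's bias. More patients would not remove it.

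**What to change.** In the Aim 1 Analysis section, replace the grouping sentence with a rule such as: *each patient is analysed in the arm given by the practice's randomised tool and the topic for which the patient was enrolled, fixed before the visit, whether or not the aid was used*. Include every enrolled patient with data on the outcome. If *use* always meant assigned use, this only makes the intent explicit. Keep a comparison by actual use, taken from the video recordings and fidelity checklist, as a labelled secondary analysis.

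In the Sample size section, state the expected uptake and say that the 80% power is conditional on full uptake.

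The cost is one sentence and an arm variable derived from assignment and topic, with no new data. The real price is power: if non-users gain nothing, it falls to about 71%, 61% and 50% at 10%, 20% and 30% non-use. That should be stated openly.
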